### Specimen collection and analysis

#### Data sources and variables

The source data are case report forms recording questionnaire data for the enrolment, third trimester and postnatal visits, and forms for laboratory and specimen results, which are stored in REDCap, a secure web-based database^30^ (online supplemental file), hosted by the Foundation for Professional Development, Pretoria, South Africa.

10.1136/bmjopen-2023-081562.supp1Supplementary data

#### Specimen collection

At the enrolment and the third trimester visits, a study nurse collects two vaginal smears using inoculation loops and air dries them on glass slides. She then collects vaginal specimens by inserting swabs into the vagina up to a mark at 4 cm and rotating around the vaginal wall. Five swabs are collected in the following order: one Cepheid GeneXpert Xpert Vaginal/Endocervical Swab in a tube with Xpert Swab Transport Reagent (Cepheid); two Qiagen digene Female Swabs in a single tube with digene Specimen Transport Medium (Qiagen, Hilden, Germany); and two dry FLOQSwabs (COPAN, Brescia, Italy) each in a separate sterile tube (figure 1).

#### Transport and storage of specimens

Vaginal smear glass slides are stored and transported in plastic slide carriers at room temperature. All vaginal swabs are initially stored at the clinic in a refrigerator (2–8°C with daily temperature checks). All vaginal swabs, except the Xpert swab, which is tested on-site, are transported on ice packs once a week by overnight road courier to the laboratory at the Department of Medical Microbiology, University of Pretoria, where they are also stored in a refrigerator until DNA extraction.

#### Microbiological analyses

The Xpert vaginal swabs are tested on-site using the Xpert CT/NG assay (Cepheid) to detect *C. trachomatis* and *N. gonorrhoeae*, as per manufacturer’s instructions. At the University of Pretoria, air-dried vaginal smears are heat fixed and Gram stained.^36^ Two qualified people record the Nugent scores (0–3: normal; 4–6: intermediate; 7–10: bacterial vaginosis) and the presence of yeasts.^37^ In case of discrepancies, a third person assesses the slide and consensus is reached by discussion. At the University of Pretoria, one vaginal FLOQSwabs is used for PCRs. The genomic DNA is extracted using the High Pure PCR Template Preparation Kit (Roche Diagnostics, Mannheim, Germany) as per manufacturer’s instructions. Real-time PCR assays are then performed using the LightCycler 480 Probes Master Kit (Roche Diagnostics) on the LightCycler 480 II instrument (Roche Diagnostics). Previously published primer and hydrolysis probe sequences and cycling conditions are used for detection and quantification of *M. genitalium*,^38^
*M. hominis*,^39^
*U. parvum*,^40^
*U. urealyticum,*^40^
*T. vaginalis*^41^ and *Candida* spp.^42 43^ The load for each assayed microorganism detected in vaginal swab specimens by real-time PCR or GeneXpert is obtained from the cycle threshold value.

#### Vaginal microbiome laboratory analyses

The vaginal swabs stored in Qiagen digene Specimen Transport Medium will be used for DNA extraction and subsequent 16S ribosomal RNA (rRNA) amplicon sequencing targeting the V3–V4 hypervariable regions for vaginal microbiota analyses at the Division of Medical Microbiology, University of Cape Town.

A commercial DNA extraction kit will be used and a bead-beating step included.^44^ A DNA isolation control will be prepared from an unused vaginal swab specimen during this process. Two PCR rounds will be conducted to prepare amplicon libraries.^45^ The aim of the first PCR round is to amplify 16S rRNA gene V3–V4 regions using the 319F 5′-ACTCCTACGGGAGGCAGCAG-3′ forward primer and 806R 5′-GGACTACHVGGGTWTCTAAT-3′ reverse primer. The aim of the second PCR round is to barcode the V3–V4 amplicons by a dual-index approach, permitting multiplexing of up to 384 samples (including controls). Amplicon concentrations for all sample libraries are measured and normalised to form a mixed loading library. The libraries will be sequenced on an Illumina MiSeq instrument (Illumina, San Diego, California, USA), 2×300 bp. To quantify the number of 16S rDNA copies per swab, a quantitative PCR using the same forward and reverse primers as described above will be used. Samples from enrolment and third trimester visits from the same woman will be processed in the same run.

#### Vaginal microbiota bioinformatics

Raw sequencing reads will be processed using an established bioinformatics pipeline.^46^ Taxonomic assignment of amplicon sequence variants will be done in DADA2^47^ with SILVA^48^ as the reference database. Vaginal microbiome composition data will be visualised in heatmaps and diagrams. For each vaginal sample, we will calculate diversity measures (alpha diversity), relative abundances and estimated concentrations of key vaginal bacteria and bacterial groups, as described.^46^ We will use the entire sequencing dataset to design vaginal microbiota types by hierarchical clustering, and each sample will be assigned to one vaginal microbiota type.

### Sample size calculation

The sample size has been calculated for objective 1, with a univariable comparison between the presence of a genital tract microorganism in the mother and gestational age at birth. Figure 2 shows that, for any vaginal or sexually transmitted microorganism, or vaginal microbiota type that has a prevalence of 10% or more among all enrolled women, about 500–600 patients provide adequate power (80%) to detect a 1-week difference (with SD 2) in mean gestational age between the two groups using Student’s t-test. Specifying an alpha of 0.83% allows for multiple hypothesis testing (six hypotheses, using a Bonferroni correction). We enrol around 600 women and aim to have complete follow-up and outcome data on at least 550 women.

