**Figure 2 F2:**
[figure not shown]
Sample size requirements at different levels of exposure prevalence with power of 80% and alpha 0.83% based on Student’s t-test. (A) SD 1.5. (B) SD 2.0. The curves for % exposed are symmetrical around a prevalence of 50%, that is, curve for 10% exposed is same as that for 90% exposed.

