#### Objective 1: association between specified exposures and pregnancy outcomes

We will examine a primary set of microorganisms as exposures, detected at either enrolment or at the third trimester visit: *M. genitalium, M. hominis*, *U. urealyticum, U. parvum, T. vaginalis* and *Candida* spp are the microorganisms for which women did not receive diagnostic tests and treatment during study visits. We will use the mean and SD for the continuous outcome (gestational age) and absolute and relative frequencies for the binary outcomes (all secondary outcomes). Gestational age at birth for each exposure will be compared using Student’s t-test and a mean difference with 95% CIs (continuous outcome) and Fisher’s exact test and a risk difference with 95% CIs (binary outcomes).To control for confounding, multivariable regression models will be fitted to all outcomes with a set of prespecified potential confounders (age, educational level, alcohol consumption, HIV infection, prior preterm birth) for all organisms. For analyses of *M. genitalium*, *T. vaginalis* and *Candida* spp, we will also control for bacterial vaginosis (Nugent score 7–10). The other genital mycoplasmas can be identified from 16S rRNA amplicon sequencing in women with vaginal dysbiosis, so are sometimes considered part of bacterial vaginosis. For these organisms, we will conduct descriptive analyses, stratified by the presence of bacterial vaginosis. For continuous confounders, a linear relationship will be assumed by default but transformations (eg, log) or more flexible approaches (eg, splines or fractional polynomials) will be considered if there is evidence for non-linearity. For the continuous outcome, we will use linear mixed-effects regression models (including data from either visit and the participant as random effect) and report the result as mean difference with 95% CIs. For the binary outcome, we will use logistic mixed-effects regression and report the result as ORs with 95% CIs.Comparisons for associations with timing of detection, other microorganism exposures and birth outcomes will be considered secondary analyses. Associations between vaginal microbiota composition and pregnancy outcomes will be assessed. We will use compositional multivariable analysis methods to identify bacterial taxa that are differentially abundant between binary pregnancy outcome groups at the level of individual taxon relative abundances. We will use mixed-effects models (with the individual participant as the random effect and including data from both visits) to assess associations between continuous and binary pregnancy outcome and the following fixed effects derived from the vaginal microbiota data: alpha diversity, vaginal microbiota types and absolute abundances of predefined bacterial groups.^46^ These models will be adjusted for confounding as described in the previous paragraph.

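### The study is sized at a Bonferroni alpha of 0.83% for six hypotheses, but the analysis section does not carry that level forward, fixes 95% CIs, and does not say which test carries each hypothesis

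*Protocol article*

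**What the plan says.** The sample size section of the protocol article sizes objective 1 on a univariable comparison of gestational age at birth between exposed and unexposed women. It says that "about 500–600 patients provide adequate power (80%) to detect a 1-week difference (with SD 2) in mean gestational age" for an exposure with a "prevalence of 10% or more among all enrolled women". It then adds: "Specifying an alpha of 0.83% allows for multiple hypothesis testing (six hypotheses, using a Bonferroni correction"). The Figure 2 caption repeats the level: "Sample size requirements at different levels of exposure prevalence with power of 80% and alpha 0.83% based on Student’s t-test". The target is given as "We enrol around 600 women and aim to have complete follow-up and outcome data on at least 550 women".

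The objective 1 analysis section says: "We will examine a primary set of microorganisms as exposures, detected at either enrolment or at the third trimester visit". It lists six: *M. genitalium*, *M. hominis*, *U. urealyticum*, *U. parvum*, *T. vaginalis* and *Candida* spp. Gestational age is compared by Student's t-test with "a mean difference with 95% CIs (continuous outcome"). The same section then fits an adjusted linear mixed-effects model to gestational age, again reported as a mean difference with 95% CIs. Timing of detection, other organisms and birth outcomes are classed as secondary. The section gives no threshold for the t-test and does not mention 0.83% or any adjustment. The opening of the statistical analysis section calls the text an overview and defers detail to a separate SAP.

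**The concern.** The article uses two error levels for the same six comparisons: 0.83% to set the sample size and 95% to report the results. For the adjusted difference, the 95% CI is the only inferential output named. A reader told that multiplicity has been allowed for will naturally take an interval that excludes zero as a finding that has passed the correction. It has not.

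Each organism also gets two analyses of the same outcome. The sizing is univariable, but confounding is controlled only in the model, and the article does not say which analysis tests the hypothesis. A correction for six hypotheses is well defined only with one test for each. At stake is whether an association reported for one of the six organisms carries the error rate that the design paid for.

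**Working it through.** **Inputs.** From the sample size section: alpha 0.83%, six hypotheses, power 80%, difference 1 week, SD 2 weeks, 10% exposed (the least favourable case covered), 600 enrolled and at least 550 evaluable. Sidedness is not stated; two-sided is assumed. That the six hypotheses are the six primary organisms is inferred from the count.

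**1. The plan's own figures.**
- Per-test alpha: 0.05/6 = 0.00833, that is 0.83%.
- Total N = (z₁₋α/₂ + z₀.₈₀)² × SD² / (difference² × p(1−p)) = (2.638 + 0.842)² × 4 / (0.10 × 0.90) ≈ 538. With whole women per group (485 unexposed) this is 539. The noncentral t calculation gives 543.
- Power at N = 550 is 81.0% (normal) or 80.7% (t).
- A one-sided test would need only 467 to 469, below the stated range, so two-sided fits.

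The stated 500–600 is reproduced.

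**2. What the correction costs.** The same design at a two-sided 5% needs 351 women (t-test). So 543 − 351 = 192 women, about a third of the total, are there because of the correction.

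**3. Family-wise error under two ways of reading the results.**

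| Rule for each of the six comparisons | Independent tests, all nulls true | Upper bound |
|---|---|---|
| 95% CI excludes zero | 1 − 0.95⁶ = 26.5% | 6 × 5% = 30% |
| p-value at or below 0.83% | 1 − (1 − 0.00833)⁶ = 4.9% | 6 × 0.83% = 5% |

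The documents give no correlation between the six test statistics. In a simulation with an assumed equal correlation of 0.2, 0.5 or 0.8, the first rule gives about 25%, 21% or 14%. The second stays below 5% throughout. If the crude and the adjusted test of each organism both counted at 0.83%, the bound would be 12 × 0.83% = 10%. The two are strongly related, so the true figure would be lower.

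**4. Intervals that match the design.** The level is 1 − 0.05/6 = 99.17%. The width ratio is 2.638/1.960 = 1.35. At N = 550 with 10% exposed, SE = 2 × √(1/55 + 1/495) = 0.284 week. The half-width is 1.960 × 0.284 = 0.56 week at 95% and 2.638 × 0.284 = 0.75 week at 99.17%.

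**5. Holm against Bonferroni.** The noncentrality for a 1-week effect is 0.5 × √(550 × 0.09) = 3.52. Simulation with six independent statistics and 10% exposed for each organism gives:

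| True 1-week effects | Power per true effect, Bonferroni | Holm | Studies where a Holm-significant organism has a 99.17% CI that includes zero |
|---|---|---|---|
| 2 | 81% | 82.5% | 4% |
| 3 | 81% | 84% | 10% |
| 6 | 81% | 92% | 49% |

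Holm is never less powerful, but it does not correspond to the 99.17% interval.

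**The case against.** The strongest objection is that family-wise error depends on the threshold applied to the p-values, not on the confidence level printed beside them. The only alpha in the article is 0.83%, and nothing says that tests are judged at 5% or that conclusions are read from the 95% CIs. Descriptive 95% CIs beside p-values judged at 0.83% are coherent. This stands. A reader might infer that the 5% family-wise rate is lost; the article does not support that, because it leaves the decision rule open.

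Second, the threshold and the choice of test are usual SAP content, and the article defers detail to an SAP that is not shown. This stands in part: the rule may be there. But the article itself prints both levels, and that mismatch can be resolved where it appears.

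Third, 26.5% is close to a worst case, and co-occurring organisms are unlikely to give independent tests. This stands, hence the range. Even 14% is well above 5%.

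Fourth, Bonferroni is valid and correctly computed. Agreed: Holm is an improvement, not the repair of an error, and its gain is small unless most effects are real.

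Fifth, the study describes its aims as exploratory. That does not remove the point, because the sample size section explicitly claims a correction.

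A reader might also fault the power statement for covering exposures beyond the six: "for any vaginal or sexually transmitted microorganism, or vaginal microbiota type that has a prevalence of 10% or more". That would be wrong. It is correct arithmetic for any exposure of that prevalence and claims no multiplicity control for microbiota types.

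**Conclusion.** The point holds as an inconsistency between design and stated analysis. The correction sets the sample size, accounting for about 190 of the 543 women needed, but the analysis section does not use it, reports at 95%, and names two analyses per organism without designating one.

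The consequence is conditional. Family-wise error is about 26% only if the 95% CI is the decision rule, all six nulls are true and the tests are independent; it is about 14% to 25% at assumed correlations of 0.8 to 0.2. It is at most 5% if one p-value per organism is judged at 0.83%. The results rest on two-sided tests and on matching six hypotheses to six organisms by count; the interval widths and power figures also assume 10% exposed for each organism. The sample size itself is sound.

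**What to change.** State in the analysis section that the six organism comparisons on gestational age at birth are the primary family, with one designated test per organism, judged at a family-wise 5%. Holm is preferable to Bonferroni because it controls the same error rate and is never less powerful.

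For the intervals, either label the 95% CIs as unadjusted for multiplicity, or add 99.17% CIs for the six primary differences. In the second case, note that these match Bonferroni and may include zero for an organism that Holm declares significant.

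The choice of designated test matters. The crude t-test is the one that was sized. If the adjusted analysis is designated, use a model with one outcome row per woman, for example a linear regression. Gestational age at birth has a single value per woman, so in a mixed model with a row for each visit the outcome cannot vary within a participant and the random effect can absorb it. Note also that the stated power refers to the univariable t-test.

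The cost is a few sentences here and in the SAP, and wider intervals for six estimates if the 99.17% CIs are added. No further participants or data are needed.

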**Figure 2 F2:**
[figure not shown]
Sample size requirements at different levels of exposure prevalence with power of 80% and alpha 0.83% based on Student’s t-test. (A) SD 1.5. (B) SD 2.0. The curves for % exposed are symmetrical around a prevalence of 50%, that is, curve for 10% exposed is same as that for 90% exposed.

#### Study timeline

Enrolment began on 28 March 2021, with an estimated date for reaching the target sample size in August 2023. Follow-up of all participants until the postnatal visit is expected to be completed by March 2024.

### Statistical analysis

This description gives an overview of the statistical methods for each objective. A detailed statistical analysis plan will be published separately and made publicly available.

We will describe the numbers of women enrolled and available at each follow-up visit in a flow chart. We will present descriptive tables of sociodemographic, behavioural and clinical characteristics and compare women with complete follow-up with those lost to follow-up.

#### Objective 1: association between specified exposures and pregnancy outcomes

We will examine a primary set of microorganisms as exposures, detected at either enrolment or at the third trimester visit: *M. genitalium, M. hominis*, *U. urealyticum, U. parvum, T. vaginalis* and *Candida* spp are the microorganisms for which women did not receive diagnostic tests and treatment during study visits. We will use the mean and SD for the continuous outcome (gestational age) and absolute and relative frequencies for the binary outcomes (all secondary outcomes). Gestational age at birth for each exposure will be compared using Student’s t-test and a mean difference with 95% CIs (continuous outcome) and Fisher’s exact test and a risk difference with 95% CIs (binary outcomes).To control for confounding, multivariable regression models will be fitted to all outcomes with a set of prespecified potential confounders (age, educational level, alcohol consumption, HIV infection, prior preterm birth) for all organisms. For analyses of *M. genitalium*, *T. vaginalis* and *Candida* spp, we will also control for bacterial vaginosis (Nugent score 7–10). The other genital mycoplasmas can be identified from 16S rRNA amplicon sequencing in women with vaginal dysbiosis, so are sometimes considered part of bacterial vaginosis. For these organisms, we will conduct descriptive analyses, stratified by the presence of bacterial vaginosis. For continuous confounders, a linear relationship will be assumed by default but transformations (eg, log) or more flexible approaches (eg, splines or fractional polynomials) will be considered if there is evidence for non-linearity. For the continuous outcome, we will use linear mixed-effects regression models (including data from either visit and the participant as random effect) and report the result as mean difference with 95% CIs. For the binary outcome, we will use logistic mixed-effects regression and report the result as ORs with 95% CIs.Comparisons for associations with timing of detection, other microorganism exposures and birth outcomes will be considered secondary analyses. Associations between vaginal microbiota composition and pregnancy outcomes will be assessed. We will use compositional multivariable analysis methods to identify bacterial taxa that are differentially abundant between binary pregnancy outcome groups at the level of individual taxon relative abundances. We will use mixed-effects models (with the individual participant as the random effect and including data from both visits) to assess associations between continuous and binary pregnancy outcome and the following fixed effects derived from the vaginal microbiota data: alpha diversity, vaginal microbiota types and absolute abundances of predefined bacterial groups.^46^ These models will be adjusted for confounding as described in the previous paragraph.

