### Participants

Inclusion criteria: Pregnant women aged 18 years or older, who live in Buffalo City Metropolitan Municipality, intend to deliver in the same municipality and provide written informed consent to take part in the study. The eligible gestational age at enrolment, confirmed by ultrasound, was below 20 weeks at the start of the study in March 2021 and was increased to 27 weeks in September 2021 to increase enrolment and to align with another trial.^29^

Exclusion criteria: Participation in any other research study or inability to understand and speak a local language (English, Afrikaans or isiXhosa).

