### Study procedures and visits

At the enrolment visit, study field workers administer a questionnaire to record sociodemographic, behavioural and clinical information in an online Research Electronic Data Capture (REDCap)^30^ software database. The study nurse examines the woman, according to the South African government standard of care.^31^ As an additional procedure, a study nurse with training in obstetric ultrasound performs an abdominal ultrasound to estimate the gestational age. If this is later than the eligibility criterion, the participant is excluded from any further study activity. A study nurse collects vaginal samples (figure 1) for on-site testing for *C. trachomatis* and *N. gonorrhoeae* using the Xpert CT/NG assay on the Gene Xpert platform (Cepheid, Sunnyvale, California, USA) and for further off-site laboratory testing (see ‘Specimen collection and analysis’).

If the test result for *C. trachomatis* or *N. gonorrhoeae* is positive, the woman receives immediate antibiotic treatment if still on-site or is contacted by telephone and asked to return to the clinic for treatment. Antibiotic treatments are first-line regimens according to South African guidelines: for *C. trachomatis*, 1 g oral azithromycin and for *N. gonorrhoeae*, 500 mg intramuscular ceftriaxone (250 mg until South African treatment guidelines for sexually transmitted infections changed in December 2022).^32^ Women with vaginal discharge syndrome but with negative Xpert test results for *C. trachomatis* and *N. gonorrhoeae* receive empirical treatment for trichomoniasis with metronidazole 400 mg twice a day for 7 days. The study nurse gives advice to women with *C. trachomatis* or *N. gonorrhoeae* on safe disclosure of her diagnosis to her partner(s) and gives her a notification slip(s) to request her partner(s) to attend a clinic for treatment.

A follow-up visit at 30–34 weeks (third trimester visit) is scheduled at which clinical and obstetric information, as well as the same vaginal specimens, is collected and treatment given, if indicated.

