### Outcomes

The primary outcome is gestational age at birth, measured in days, based on the ultrasound assessment at the enrolment visit. Secondary outcomes are preterm birth (<37 completed weeks of gestation), low birth weight (birth weight <2500 g), miscarriage (dead fetus delivered before 28 completed weeks of pregnancy or with birth weight below 1000 g) and stillbirth (dead fetus delivered at or after 28 completed weeks of pregnancy or with birth weight above 1000 g).^33 34^ We chose gestational age at birth as the primary outcome because, while the cut-off of 37 weeks is the standard definition of preterm birth, dichotomisation of a continuous variable results in a loss of statistical power.^35^

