#### Objective 3: classification and regression tree analysis for the primary outcome

We will conduct exploratory analyses to examine the combination of microorganisms that best predicts earlier gestational age at birth using classification and regression tree analysis.^50^ This method belongs to the family of decision tree machine learning algorithms and allows for non-parametric analyses of a large number of binary, categorical or continuous predictors. They are typically easy to interpret and can detect predictors with small marginal effects when there are strong interaction effects. We will make use of the predictive potential for gestational age at birth of all sexually transmitted and genital tract microorganisms, including individual bacterial taxa or bacterial groups identified by 16S rRNA gene amplicon sequencing (as binary or continuous variables) and confounding variables identified in objective 1. We will present variable importance scores and curves of marginal effects to show how prediction of the outcome changes at different levels of the exposure of each variable in the model. To avoid overfitting, we will consider bootstrap aggregating via random forests.^51^

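### The primary exposure rule depends on the outcome: only pregnancies that reach 30–34 weeks get a second chance to be classed as exposed, which biases the unadjusted comparisons towards later birth in exposed women

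*Protocol article*

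**What the plan says.** All references are to the protocol article.

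- **Exposure** (Objective 1): "We will examine a primary set of microorganisms as exposures, detected at either enrolment or at the third trimester visit". The set is six organisms that were not tested for and treated at study visits. Associations with the timing of detection are placed among the secondary analyses, so the primary contrast pools the two visits.
- **Sampling times** (Participants; Study procedures and visits): the gestational age limit at enrolment "was below 20 weeks at the start of the study in March 2021 and was increased to 27 weeks in September 2021". "A follow-up visit at 30–34 weeks (third trimester visit) is scheduled", and the vaginal specimens are taken again then.
- **Outcomes** (Outcomes): "The primary outcome is gestational age at birth, measured in days, based on the ultrasound assessment at the enrolment visit". Among the secondary outcomes, miscarriage is, by its gestational criterion, a "dead fetus delivered before 28 completed weeks of pregnancy", with a birth-weight alternative.
- **Analysis** (Objective 1): Student's t-test for gestational age and Fisher's exact test for binary outcomes, then mixed-effects regression on records from the visits with a participant random effect, adjusted for prespecified confounders.

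No landmark, time-updated exposure or delayed entry is described, and the limitations in the Discussion do not mention the point.

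**The concern.** Under the stated rule, exposure status is partly decided by how long the pregnancy lasts, and that is the outcome. A miscarriage before 28 weeks, or a birth before the second visit, is classified on one sampling. A pregnancy that continues is classified on up to two. A woman first found positive at the second visit has, by construction, carried to at least 30 weeks. This is immortal-time bias.

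It works against the study hypothesis and is concentrated in the earliest losses. Adjusting for age, education, alcohol, HIV and prior preterm birth does not remove it, because it comes from how exposure is assigned and not from confounding. At stake are some attenuation of the primary comparison and a larger distortion of the miscarriage comparison.

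**Working it through.** **The plan's own figure.** Inputs (Sample size calculation): difference 1 week, SD 2, 10% exposed (1:9), power 80%, alpha 0.83% (0.05/6; two-sided assumed).

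Unexposed n = (2.64 + 0.84)² × 2² × (1 + 9) / 1² ≈ 485; total = 485/0.9 = 539. With the t distribution, power is about 80% at 540 women and 81% at 550. This lies within the stated 500–600 and is not in dispute.

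**Notation.** The article gives none of these values; all are assumed and shown as ranges.
- p1: prevalence at enrolment
- p2: proportion of enrolment-negatives newly positive at the second visit
- f: proportion delivering before that visit
- D: gap in mean gestational age between women who do and do not reach it

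**Miscarriage or any birth before the visit, no true effect.** Exposed proportion is p1 among early losses and p1 + (1 − p1)p2 among women sampled twice.
- p1 = 10%, p2 = 5%: 0.10 + 0.90 × 0.05 = 0.145; OR = (0.10/0.90)/(0.145/0.855) = 0.66.
- p1 = 10%, p2 = 10%: 0.10 + 0.90 × 0.10 = 0.19; OR = (0.10/0.90)/(0.19/0.81) = 0.47.

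These do not depend on f. The Introduction cites summary ORs of about 1.3–2.0. A true OR of 1.3 would appear as about 0.62–0.85, and a true OR of 2.0 as about 0.95–1.31.

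**Mean gestational age, no true effect.** Bias = D × [P(early | unexposed) − P(early | exposed)], where
- P(early | exposed) = p1·f / {p1·f + [p1 + (1 − p1)p2](1 − f)}
- P(early | unexposed) = f / {f + (1 − p2)(1 − f)}

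Example with f = 2%, D = 8, p1 = 10%, p2 = 5%: 0.002/0.1441 = 0.0139 and 0.02/0.951 = 0.0210; bias = 8 × 0.0072 = +0.06 week.

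The last column is √[f(1 − f)] × D, the SD that the early/late split creates before any ordinary variation. It should stay below the planned SD of 2.

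| f | D (weeks) | bias, p2 = 5% | bias, p2 = 10% | SD from split |
|---|---|---|---|---|
| 2% | 8 | +0.06 | +0.09 | 1.12 |
| 2% | 12.4 (27 v 39.4) | +0.09 | +0.14 | 1.74 |
| 5% | 8 | +0.14 | +0.23 | 1.74 |
| 10% | 8 | +0.27 | +0.44 | 2.40 |
| 5% | 17.4 (22 v 39.4) | +0.30 | +0.49 | 3.79 |

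The last two rows contradict the planned SD. The 5%, 8-week row sits at the limit and, against the cited preterm incidence of about 10%, would need half of all preterm births to precede the visit.

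**Simulation, no true effect** (second visit uniform over 30–34 weeks; 100% or 85% attendance).
- Skewed distribution (mean 38.8, SD 2.2, 9.7% preterm, 1.8% delivered before the visit; p1 5–50%, p2 5–30%): bias +0.06 to +0.14 week, spurious preterm OR about 0.89–0.95. Enrolment-only exposure gives no difference beyond simulation noise (±0.05 day).
- Exactly normal, mean 39, SD 2: 0.1% deliver before the visit and the bias is below 0.01 week. That shape implies about 16% preterm, above the cited 10%.

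**Simulation, true 1-week harm.** For (p1, p2) = (5%, 5%), (10%, 5%), (10%, 10%), (30%, 20%):
- Later detections equally harmful: the two-visit rule gives −0.87, −0.91, −0.86, −0.86 week. Enrolment-only gives −0.95, −0.95, −0.90, −0.80, roughly −(1 − p2), because affected later acquisitions sit in the unexposed group.
- Later detections harmless: the two-visit rule gives −0.40 to −0.62; enrolment-only gives about −0.98 to −1.00.

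**The case against.** The strongest reply is that the effect on the primary outcome is small, that visit-specific results will exist as secondary analyses, and that the Discussion presents the study as generating hypotheses. The first part stands: on assumptions that fit the planned SD the bias is around 0.1 week. The secondary timing analyses, however, leave the primary contrast as it is.

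Enrolment-only exposure also has a price. It counts later acquisitions as unexposed, and where these are common and equally harmful (30% at enrolment, 20% new) it attenuates slightly more than the two-visit rule (0.80 against 0.86 week). What it preserves is a correct null.

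A reader might infer more than the article supports:

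- *That organisms would look protective in the primary analysis.* Apparent protection arises if there is no effect, or for miscarriage at modest true ORs. A 1-week harm stays a harm.
- *That the bias could reach half of the 1-week target.* This needs about 5% early deliveries at a mean of 22 weeks, which alone implies an SD of 3.79.
- *That the adjusted mixed model is biased in the same direction.* There, early deliverers contribute enrolment records only, and the direction depends on how prevalence changes between visits.
- *That women who miss the second visit are counted as unexposed.* The article does not say so, and a woman positive at enrolment is exposed either way.
- *That the regression tree leaks the outcome.* Objective 3 uses the "predictive potential for gestational age at birth of all sexually transmitted and genital tract microorganisms" but does not say which visit's values enter or how missing ones are coded.

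**Conclusion.** The point holds in a limited form. As written, the primary exposure depends on the outcome, and the unadjusted t-test and Fisher comparisons are biased towards later birth in exposed women whenever the second visit brings new detections.

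For miscarriage, a secondary outcome, or any birth before the visit, the spurious OR is about 0.66–0.47 at an assumed 10% enrolment prevalence and 5–10% new detections. For mean gestational age the bias is about +0.06 to +0.14 week with roughly 2% delivering before the visit. It is negligible if gestational age is exactly normal with SD 2. It is larger only if more women deliver early or if miscarriages enter that analysis, which the article does not state. A true 1-week harm, shared by later detections, would be attenuated to about 0.86–0.91 week and not reversed. The direction in the visit-level mixed model cannot be fixed from the article. The sample size calculation itself is sound.

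**What to change.** - Make detection at enrolment the primary exposure for all women.
- Analyse third-trimester detection, separating new from persistent, only as a landmark analysis among women undelivered and sampled at that visit. Alternatively, treat it as a time-updated exposure in a survival model on the gestational-age scale with delayed entry at enrolment, which also handles the differing enrolment ages.
- If third-trimester values are used in objective 3, restrict that analysis to the landmark set.

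The cost is a change of wording in the protocol and analysis plan, using data already being collected. Fewer women count as exposed, and later acquisitions are addressed only in the landmark or time-updated analysis. The stated 80% power (about 81% with 550 women and SD 2) then applies only to organisms with at least 10% prevalence at enrolment.
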